### Health economic evaluation

#### Aims and objectives

The aim of the health economic evaluation is to provide evidence to inform decisions about the potential wider implementation of the intervention. While the ultimate decision is a political one, health economic analysis offers robust scientific insights to support informed policymaking.

Standard criteria for health economic evaluations will be assessed. To justify implementation into routine care, the intervention should meet at least one of the following conditions:

The PARTNER intervention reduces healthcare costs for statutory health insurance (SHI) without negatively impacting patients’ quality of life.The PARTNER intervention improves patients’ quality of life without increasing healthcare costs.The PARTNER intervention enhances quality of life, with associated healthcare cost increases deemed acceptable within cost-effectiveness thresholds.

#### Study design

Primary outcomes from biometric analysis, such as reductions in the DBI and changes in the incidence of falls, will be compared between the control group and intervention group. Furthermore, for all study participants, health-associated quality of life is derived from the EQ-5D-5L questionnaire. Based on that, we compute the EQ-5D index as a summary statistic that is used to compare life quality developments between the IG and the CG. These outcomes will then be analyzed alongside corresponding changes in healthcare costs for both groups. We approximate those based on the study participants self-reported healthcare utilization and up-to-date respective unit costs for Germany. A detailed description of the methodological approach is given below.

#### Data collection and outcome measures

Table 10 outlines health economic outcomes (HEO1 to HEO5), including the cost and benefit endpoints considered in the analysis.

*Health-related utility*: Health-related utility is measured across five dimensions:

*DBI*: Calculated based on patient interviews.*EQ-5D index*: Measures health-related quality of life using data from the EQ-5D-5L questionnaire, deriving a summary statistics from time-tradeoff analysis.^37,42^*EQ-VAS*: Measures health-related quality of life using data from the EQ-5D-5L questionnaire based on a visual analog scale.*Incidence of falls*: Captured through patient diaries.Cognition index: Assessed via a VFT.

*Cost analysis*: Intervention costs are categorized into *direct* and *indirect* costs:

*Direct costs* are estimated based on documented expenses for informational materials and the time invested by GPs, nursing staff, and pharmacists related to the intervention. Time units are multiplied by corresponding cost units, derived from current reports and published unit costs.*Indirect costs* are assessed by collecting data on healthcare utilization over 3-month periods for both study groups. This includes physician visits, outpatient or inpatient hospital care, and physical or occupational therapies. Data is gathered using a validated questionnaire for Germany.^39,40^ Healthcare utilization is then multiplied by cost units, as done for direct cost estimation.

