##### Rationale and components of the PARTNER intervention arm

The PARTNER intervention has been designed to address key barriers to deprescribing PSA-PIMs. One such barrier is inertia, that is, in this context, a reluctance to deprescribe PSA-PIMs without an acute reason, such as ADRs.^24,25^ At the level of healthcare professionals, this is exacerbated by competing priorities, time pressure, and a lack of knowledge on how best to deprescribe (e.g., the design and practical implementation of tapering schemes) as well as patient resistance.^26,27^ The latter can be fueled by patient misconceptions about the benefits and risks of PSA-PIMs.^
28
^ To overcome these barriers, the PARTNER intervention includes components aiming to educate and motivate healthcare professionals (via a web-based continuing professional development (CPD) portal and a moderated live CPD session) as well as patients (via empowerment brochures). In addition, there are components aiming to facilitate its practical implementation via tools, interprofessional case conferences, and delegation of patient empowerment to community pharmacies.

GPs and pharmacists volunteer to participate and to implement either the PARTNER intervention or the control intervention. While no financial incentives are provided as components of the intervention itself, GPs and pharmacists are compensated for their time and effort. Specifically, GP practices and community pharmacies in the intervention group receive €180 per patient enrolled in their cluster, while those in the control group receive €120 per patient. The higher compensation in the intervention group reflects the additional time, documentation requirements, and complexity associated with the intervention. Participating providers in the intervention group are required to complete a short questionnaire for each intervention component, enabling monitoring of compliance with the study protocol. However, it is important to note that the study protocol does not compel participants in either arm to undertake a deprescribing attempt.

Table 3 maps the intervention components to specific functions and elements of the COM-B model.^
29

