The interprofessional workshop aims to deepen, focus, and strategically plan the collaboration between GP practices and community pharmacies of each cluster randomized to the intervention arm. In preparation for the workshop, clusters are asked to familiarize themselves with the resources provided in the web-based portal (see above), and GPs are asked to provide community pharmacists with relevant clinical information on included patients using standardized templates (medication, diagnoses, selected laboratory results). The workshop itself has a planned duration of up to 2 h and consists of two parts. Part 1 (intervention training) is moderated by the study team. The session aims to ensure that GP practices and community pharmacies understand the rationale behind the intervention’s focus on PSA-PIMs. It facilitates introductions between team members, clarifies their respective roles and responsibilities, and familiarizes participants with the resources and tools available on the web-based portal. This component is designed to be flexible, allowing the study team to adapt the content and emphasize topics of particular relevance to each cluster. Part 2 (case conference), which is conducted independently of the study team, enables GPs and community pharmacists to discuss each study patient. Together, they decide whether deprescribing should be attempted and identify specific drugs to target for deprescribing. This structured yet adaptable approach ensures that each cluster is equipped to collaborate effectively while tailoring the intervention to meet their unique needs.

Empowerment brochures (patient level).

In the PARTNER intervention arm, the GP practice sends drug-specific and layperson-friendly empowerment brochures to patients selected in the interprofessional workshop (see above), unless the respective GP and pharmacist concluded that PSA-PIM deprescribing should not be attempted for a specific patient. To encourage patients to engage with the brochure, each patient also receives a personalized letter from their GP practice asking them to read the brochure at home and bring it along to their pharmacy visit. Seven different brochures with a focus on the following drugs and indications are available:

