HEO3	Quality of life (EQ-VAS)	- Provision of remedies and aids - Outpatient care/rehabilitation	T_0_, T_1_, T_2_, T_3_, T_4_
HEO4	Falls (Patient Diary)	- Resources GP practice/pharmacy (personnel, infrastructure, and material)	T_1_, T_2_, T_3_, T_4_
HEO5	Cognition (Verbal Fluency Test Score)		T_0_, T_2_, T_4_

* Data collection for T_0_ is at randomization. T_1_, T_2_, T_3_, and T_4_ are defined as 3, 6, 9, and 12 months after the pharmacy consultation in each arm, respectively. In case the pharmacy consultation does not take place within 3 months after randomization (protocol deviation), T_1_, T_2_, T_3_, and T_4_ are defined as 6, 9, 12, and 15 months after randomization.

EQ-5D-5L, EuroQol 5-Dimension 5-Level questionnaire; EQ-VAS, EuroQol Visual Analogue Scale; HEO, health economic outcomes.

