#### Research questions

Table 11 outlines the distinct research questions addressed by the process evaluation, investigated using both quantitative and qualitative methods.

**Table 11. table11-20420986251400042:** Overview of research questions to be examined by the process evaluation of the PARTNER cluster-randomized trial by intervention level and process step.

Process step	Research question(s)	Themes and parameters to be examined qualitatively or quantitatively (data collection from “main study” documents or bespoke “process evaluation”)
Cluster level		
Recruitment of clusters	How were clusters recruited?	Qualitative (inductive and deductive): Procedure and deviations, preselection, reasons for (non-) participation, support from study staff (process evaluation)
		Quantitative: Recruitment rate: proportion (%) of participating/invited doctors and pharmacists (main study)
	. . . how high is the willingness to participate?	Quantitative: Recruitment rate: proportion (%) of participating/invited GPs and pharmacists (main study)
	. . . what reasons play a role in participation?	Qualitative (inductive): Reasons for participation/non-participation (process evaluation)
	. . . who is taking part in the study?	Quantitative: Comparison of characteristics of participants/non-participants (main study)
Intervention delivery and response	. . . how were the intervention components implemented by the study staff?	Qualitative (inductive): Experience of the study staff from the training courses, level of knowledge, and previous experience of the doctors and pharmacists, necessary deviations from the specified procedure (process evaluation)
		Quantitative: type, number, and “severity” of deviations (main study)
	. . . what support was required to enable the service providers to implement the intervention components?	Qualitative: Type and effort of support provided by study staff (process evaluation)
		Quantitative: Number of contacts between study personnel and service providers (main study)
	. . . how are intervention components implemented?	Quantitative: Descriptive (number/type of empowerment brochures per patient; main study)
		Quantitative: Number/spectrum of identified ABPs in medication analyses (main study)
		Quantitative: Number of doctor/pharmacist contacts per patient (main study)
		Quantitative: Proportion (%) of patients with ⩾1 deprescribing attempt (main study)
		Quantitative: Number of (PSA-PIM-related) contacts with doctor/pharmacist (main study)

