### Implications for healthcare practice and research

The PARTNER trial’s focus on comprehensive educational resources and practical tools for healthcare providers highlights the need for ongoing professional development in managing complex medication regimens. The emergence of deprescribing networks and guidelines in several countries is an important development in this regard. However, practical tools equipping professionals and patients to plan and implement deprescribing processes may additionally be required to increase their confidence and efficacy in deprescribing.

In addition to better equipping healthcare professionals and patients deprescribing, the PARTNER trial evaluates the potential benefits of closer interprofessional collaboration between GPs and pharmacists in deprescribing efforts. Given the widening gap between healthcare supply and demand, it will be essential to fully utilize the knowledge and skills of all healthcare professionals and to develop models to integrate their efforts, which is particularly relevant in healthcare systems where primary healthcare providers operate in silos. The PARTNER trial tests one such collaborative model within the context of this trial, where collaboration is facilitated by the research team. If shown to be effective, further research should develop and test strategies (such as financial incentives for both GPs and pharmacists) to motivate such collaboration without the need for external facilitation.

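### The direct-cost rule lists materials and GP-practice and pharmacy resources but not the study team's moderation of the workshop, so as written it pairs the effect of a facilitated intervention with the cost of an unfacilitated one

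*Protocol article*

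**What the plan says.** The cost analysis (Health economic evaluation, Data collection and outcome measures) builds direct costs from two items: "documented expenses for informational materials" and "the time invested by GPs, nursing staff, and pharmacists related to the intervention". Time is then multiplied by published unit costs. Table 10 draws the same boundary; its provider-side item reads "Resources GP practice/pharmacy (personnel, infrastructure, and material").

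The section on the rationale and components of the PARTNER arm describes who delivers the intervention. Healthcare professionals are educated and motivated "via a web-based continuing professional development (CPD) portal and a moderated live CPD session". Of the interprofessional workshop it says "The workshop itself has a planned duration of up to 2 h and consists of two parts", and "Part 1 (intervention training) is moderated by the study team". Part 2, the case conference, runs without the study team. Table 4 ticks the research team for the workshop, places it once, two weeks before the pharmacy consultation, and marks it as intervention arm only.

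The Discussion (Implications for healthcare practice and research) describes the trial as a setting "where collaboration is facilitated by the research team". It leaves to further research how such collaboration could be motivated without outside help.

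The Statistical analysis subsection of the economic evaluation takes the perspective of the statutory health insurance (SHI) community. It bases the recommendation on routine implementation mainly on the cost-effectiveness analysis for the EQ-5D index.

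**The concern.** An economic evaluation alongside a trial should cost the same intervention that produced the effect. Here the effect comes from clusters whose GPs and pharmacists were trained in a session moderated by the study team, which adapts the content to each cluster. That is delivery of a named component, not a research task such as randomisation or data collection. Neither cost list has a place for it.

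Because the session exists only in the intervention arm, leaving it out cannot cancel between arms. It enters the cost comparison first and the ICER afterwards. All three conditions that the plan sets for justifying implementation involve cost: falling costs, costs that do not rise, or a cost increase within an acceptable threshold. If the cost difference is near zero or the ICER near a threshold, a modest one-sided omission could matter.

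**Working it through.** **1. Components against cost items**

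| Component | Delivered by | In the listed direct costs? |
|---|---|---|
| Web portal and educational material | Study team provides; GPs and pharmacists use | Materials and provider time: yes |
| Workshop Part 1 | Study team moderates; GPs and pharmacists attend | Provider time: yes. Moderator time: not listed |
| Workshop Part 2 | GPs and pharmacists | Yes |
| Empowerment brochures | GP practice | Yes |
| Pharmacy consultation (both arms) | Pharmacist | Yes |
| GP consultation | GP | Yes |

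Moderator time in Part 1 is the clear gap, together with any delivery-related support from study staff. Study training is a different activity: Table 4 places it before randomisation and does not restrict it to the intervention arm.

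**2. Timing.** Table 4 puts T0 at minus 1 month and the workshop at minus 2 weeks. The input therefore falls inside the T0 to T4 period over which the ICER is computed.

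**3. Direction.** Let m ≥ 0 be the unlisted delivery cost per intervention patient; it is zero in the control arm.

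- Incremental cost as tested = incremental cost from the listed items + m.
- With cost in the numerator and a utility gain ΔU > 0, the ICER is too low by m/ΔU.
- The plan's text calls cost the numerator, but the printed formula puts utility over cost. In that form, with both increments positive, utility per euro is too high. Either way the omission favours the intervention.

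**4. Size.** The document states no intervention cost, moderator hours or staff rate, so there is no figure to reproduce. Patients per cluster come from the Sample size section: 264 / 0.75 = 352, and 352 / 44 clusters = 8.

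m = moderators × hours each × hourly rate / patients per cluster. All but the last input are assumptions; hours include preparation and any travel.

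- Low: 1 × 1 × 40 / 8 = EUR 5 per trial patient (EUR 40 per cluster).
- High: 2 × 3 × 70 / 8 = EUR 52.50 per trial patient (EUR 420 per cluster).

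Other inputs shift the range:

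- Moderation alone, at 1 to 2 person-hours and EUR 50 to 100 per hour: 50 / 8 = EUR 6.25 to 200 / 8 = EUR 25.
- As much as 8 person-hours per cluster, including support, at EUR 100: 800 / 8 = EUR 100.
- The EUR 40 to 420 per cluster spread over 15 patients, the most a practice is told to recruit: EUR 2.70 to 28.
- The same spread over an assumed 40 present and later patients: EUR 1 to 10.50.

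**5. What cannot be computed.** The relative bias in the ICER needs the incremental cost, which also contains inpatient, outpatient, drug and other utilisation costs through T4. None of these is known.

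**The case against.** The best defence is that one summary sentence and one table cell in a journal article are not a full cost inventory. Nowhere does the article say that moderation is left out or valued at zero, and the full protocol or economic plan may include it. That stands as a limit on certainty. But the article does state its costing rule, twice and consistently, and the point concerns that stated rule.

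The second defence is that the authors treat outside facilitation as a feature of the trial, look ahead to collaboration without it, and take the SHI perspective. Costing only practice and pharmacy resources is then a defensible picture of roll-out. That supports a scenario. It does not supply an effect estimate for unfacilitated collaboration, which this trial does not test.

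Some stronger readings are not supported:

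- A reader might infer a recurring cost. Table 4 shows one workshop per cluster, and only Part 1 of a session of up to 2 hours is moderated.
- A reader might set the assumed cost against the gap in provider compensation (EUR 180 versus EUR 120 per patient) and read the share as bias in the ICER. The plan values time by unit costs, and the payment gap also reflects documentation, so the comparison says nothing about the ICER.
- A reader might infer from Table 11 that the hours will be on record. It plans a count of contacts between study personnel and providers and a qualitative account of support effort; neither gives hours.

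**Conclusion.** The point holds as a minor one. Followed as written, the direct-cost rule omits a delivery input that exists only in the intervention arm, and the omission works in the intervention's favour. The direction follows from the design. The size does not: roughly EUR 5 to 50 per trial patient rests on assumed moderators, hours and rates with 8 patients per cluster. It rises with more support time and falls if the one-off training serves later patients. It would be too strong to say that the reported ICER will be wrong by a known amount, or that the plan deliberately excludes this time, because the document establishes neither. An ICER is also computed only if neither alternative clearly dominates, although the preceding cost comparison would carry the same omission.

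**What to change.** In the economic analysis plan, add to direct costs the study-team hours spent on moderating Part 1 and on delivery-related support, valued at a staff unit cost in the same way as provider time. Exclude research tasks: study training, randomisation and data collection. Use this as the analysis of the intervention as tested. Report the ICER without external facilitation as a labelled roll-out scenario, and state that its effect estimate still comes from facilitated clusters.

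The cost is one line in the plan and a short time log, or a retrospective estimate for workshops already held, because the planned records do not give hours. The ICER will look slightly less favourable to the intervention.

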#### Statistical analysis

The health economic evaluation follows a three-step procedure previously recommended for health economic analyses in Germany.^
47
^ Cost analysis employs a *difference-in-differences* (DiD) approach to compare trends in individual healthcare cost estimates between the intervention group and the control group, incorporating both direct and indirect costs.

In the first step, utility analysis is conducted using the DiD method to compare changes across the five utility dimensions at the individual level. Utility differentials are calculated between the four survey periods and subsequently compared between the IG and CG using hypothesis testing. For instance, for a patient *i*, the first differences in some utility index between periods 0 and 1 are

$$\Delta u_{i,1}:=u_{i,1}-u_{i,0},$$

With *μ*_i,0_ being the observation for the respective utility index at *T*_0_ for patient *i*. We check the null hypothesis that the utility differentials are not associated with whether the patients belong to the IG or the CG, that is, for

$$\Delta u_{i,t}=\delta I+\beta \prime x_{i},$$

we check

$$H_{0}:\delta =0.$$

Here, *I* is a binary variable that takes the value 1 for patients of the IG and 0 for those in the CG. **
*x*
**_i_

$x_{i}$
 is a vector of sociodemographic predictors. Those are included to avoid a potential bias in the test results because of heterogeneities between the two study groups. If the null hypothesis of interest can be rejected, the intervention is associated with different utilities than the standard treatment. The Greeks are parameters estimated based on the data via ordinary least squares.

If the intervention does not lead to a deterioration in health utility, cost analysis will estimate cost differentials between the intervention and control groups using an approach similar to that applied for the utility dimensions. If the initial steps of the analysis do not demonstrate clear dominance of one care alternative over the other (i.e., neither intervention nor control prevails), cost-effectiveness analysis will be conducted, computing an incremental cost-effectiveness ratio (ICER). Analysis is conducted from the perspective of the SHI community, with the time horizon covering at least the study observation period. To address statistical uncertainty, stochastic sensitivity analyses will be performed using Monte Carlo simulations. These simulations generate empirical distributions of the ICER by simulating utility and cost indices 10,000 times. This approach provides an ICER distribution that can be used to estimate the probability of the intervention meeting prespecified cost-effectiveness thresholds, similar to methods described in Gillespie et al.^
48
^

ICERs will be calculated for all five utility dimensions to provide a comprehensive basis for healthcare decision-making. However, given the recognized importance of the EQ-5D index in health economic evaluations, recommendations for implementing the intervention into standard care will be primarily based on its cost-effectiveness analysis. The Monte Carlo simulations generate empirical distributions for both the utility (denominator) and cost (numerator) components of the ICERs based on 10,000 simulations of the overall cost and utilities change associated with the intervention through the observed period *T*_0_–*T*_4_. The nuisance parameters used for this are estimated by the earlier-mentioned regression models. For instance, the ICER in the trajectory *s* is:

$${\mathrm{ICER}}_{s}=\frac{\Delta u_{0-4,s,\mathrm{IG}}-\Delta u_{0-4,s,\mathrm{CG}}}{\Delta c_{0-4,s,\mathrm{IG}}-\Delta c_{0-4,s,\mathrm{CG}}},$$

with

$\Delta \mu_{0–4,s,\mathrm{IG}}$
: average utility differential between *T_0_* and *T_4_* for intervention group in trajectory *s*,
$\Delta \mu_{0–4,s,\mathrm{CG}}$
: average utility differential between *T_0_* and *T_4_* for control group in trajectory *s*,
$Dc_{0–4,s,\mathrm{IG}}$
: average cost differential between *T_0_* and *T_4_* for intervention group in trajectory *s*,
$Dc_{0–4,s,\mathrm{CG}}$
: average cost differential between *T_0_* and *T_4_* for control group in trajectory *s*.

This approach generates a non-parametric distribution for the ICER, which can be compared directly to predefined cost-effectiveness thresholds and provide a recommendation, if the implementation of the intervention is given some willingness to pay.

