* Data collection for T_0_ is at randomization. T_1_, T_2_, T_3_, and T_4_ are defined as 3, 6, 9, and 12 months after the pharmacy consultation in each arm, respectively. In case the pharmacy consultation does not take place within 3 months after randomization (protocol deviation), T_1_, T_2_, T_3_, and T_4_ are defined as 6, 9, 12, and 15 months after randomization.

EQ-5D-5L, EuroQol 5-Dimension 5-Level questionnaire; SO, secondary outcomes.

**Table 9. table9-20420986251400042:** Secondary outcomes—clinical outcomes.

No.	Source population	Parameter	Time of measurement*
SO21	All study participants	Number of falls (reported in fall diaries) in source population	• T_1_, T_2_, T_3_, T_4_
SO22	All study participants	Number of emergency hospital admissions due to falls in source population	• T_1_, T_2_, T_3_, T_4_
SO23	All study participants	Number of adverse drug reactions in source population	• T_0_, T_2_, T_4_

* Data collection for T_0_ is at randomization. T_1_, T_2_, T_3_, and T_4_ are defined as 3, 6, 9, and 12 months after the pharmacy consultation in each arm, respectively. In case the pharmacy consultation does not take place within 3 months after randomization (protocol deviation), T_1_, T_2_, T_3_, and T_4_ are defined as 6, 9, 12, and 15 months after randomization.

SO, secondary outcomes.

Hospitalizations, use of medical services, and quality of life estimates are collected at all five time points. Falls/fall injuries, hospital admissions (with outpatient or inpatient care), and contacts with GPs or specialist doctors are also documented in patient diaries to minimize recall bias. The use of a patient diary is regularly checked by study personnel. All other endpoints are recorded at T_0_, T_2_, and T_4_ (see Tables 5–10). Participant retention and complete follow-up are promoted by the regular phone calls (in intervals of 3 months) to collect primary and secondary outcome data. In case of study discontinuation, the stated reason(s) will be documented.

**Table 10. table10-20420986251400042:** Health economic outcomes.

No.	Benefit	Cost	Time of measurement*
HEO1	Primary Outcome (reduction in Drug Burden Index of ⩾0.15)	Questionnaire for Health-Related Resource Use in an Elderly Population (FIMA):	T_0_, T_2_, T_4_
HEO2	Quality of life (EQ-5D-5L Score)	- Outpatient medical care - Inpatient medical care - Drug costs	T_0_, T_1_, T_2_, T_3_, T_4_

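### The economic regressions subtract the T0 value but do not adjust for it; adding T0 as a covariate would gain precision at no cost

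*Protocol article*

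**What the plan says.** The Statistical analysis section of the Health economic evaluation writes the utility model out. For a patient i, "the first differences in some utility index between periods 0 and 1 are" the T1 value minus the T0 value. This change is regressed on an arm indicator and on x_i, which "is a vector of sociodemographic predictors. Those are included to avoid a potential bias in the test results because of heterogeneities" between the arms. On estimation it says: "The Greeks are parameters estimated based on the data via ordinary least squares".

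For costs, "cost analysis will estimate cost differentials between the intervention and control groups using an approach similar to that applied for the utility dimensions". On the Monte Carlo ICER it says: "The nuisance parameters used for this are estimated by the earlier-mentioned regression models". The ICER itself is built from differentials between T0 and T4. Of the EQ-5D index it says that "recommendations for implementing the intervention into standard care will be primarily based on its cost-effectiveness analysis".

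Tables 4 and 10 show which T0 values exist. Resource use, EQ-5D index and EQ-VAS are collected at T0 to T4, and the Verbal Fluency Test at T0, T2 and T4. Falls are listed from T1 on only.

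**The concern.** Subtracting T0 amounts to using it as a covariate with its slope fixed at 1. The slope that best predicts follow-up from T0 is rho times the ratio of the follow-up SD to the T0 SD. With equal SDs this is simply rho, which is below 1. A fixed slope of 1 therefore carries surplus T0 noise into the outcome. It also over-corrects when the arms happen to differ at T0.

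The section includes x_i to guard against differences between the arms. The baseline variable closest to the outcome is its own T0 value, and that is not in x_i. Sociodemographic variables may explain part of it but do not replace it. The primary GLMM, by contrast, does adjust for T0 type and number of PSA-PIM.

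At stake are the precision of the cost and utility contrasts and the spread of the simulated ICERs on which the implementation advice leans.

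**Working it through.** **Inputs from the protocol article (Sample size).** 22 clusters per group, 6 analysed patients per cluster, ICC 0.05, 264 analysed and 352 recruited. The article states no power or precision figure for the economic analysis.

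**Check of the stated sample size.** The design effect is 1 + (6-1) x 0.05 = 1.25. For 10% versus 25%, with unpooled variance, two-sided alpha 0.05 and a noncentral t on 2k-2 degrees of freedom (k clusters per arm), power is 79.7% at 21 clusters per arm and 81.6% at 22. So 22 clusters per arm and 264 patients reproduce, and 264 / 0.75 = 352. The economic analysis then rests on about 132 patients per arm.

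**Assumptions, not in the article.** rho between T0 and follow-up (given x_i) is 0.3 to 0.7. The SD ratio k = s0/s1 (T0 over follow-up) is 0.7 to 1.3. The ICC of 0.05, set for the primary endpoint, is carried over to cost and utility.

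**1. Residual variance, with s1 = 1.**
- Change score: 1 + k² - 2·k·rho
- T0 as covariate: 1 - rho²
- Difference: (k - rho)², never negative, so in large samples adjustment is never less precise.

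**2. Equal SDs (k = 1).** The ratio is 2(1-rho)/(1-rho²) = 2/(1+rho).

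| rho | change | adjusted | variance ratio | excess SE |
|---|---|---|---|---|
| 0.3 | 1.40 | 0.91 | 1.54 | 24% |
| 0.5 | 1.00 | 0.75 | 1.33 | 15% |
| 0.7 | 0.60 | 0.51 | 1.18 | 8% |

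The follow-up value alone has variance 1. Below rho 0.5 the change score is therefore noisier than ignoring T0 altogether.

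**3. Unequal SDs (variance ratio).**

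| k | rho 0.3 | rho 0.5 | rho 0.7 |
|---|---|---|---|
| 0.7 | 1.18 | 1.05 | 1.00 |
| 1.3 | 2.10 | 1.85 | 1.71 |

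**4. Effect of a chance T0 imbalance.** With equal SDs the change-score contrast shifts by -(1-rho) per unit of imbalance. The SD of the imbalance is sqrt(2 x 1.25 / 132) = 0.14 SD units, with a 95% range of about ±0.27. At rho 0.5 a typical shift is 0.5 x 0.14 = 0.07 SD, and the edge of the 95% range gives about 0.13 SD.

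**5. Simulation.** With 22 clusters per arm, 6 patients each, ICC 0.05, equal SDs and 4000 runs, the variance ratios were 1.56, 1.37 and 1.17 at rho 0.3, 0.5 and 0.7. The slopes of the change-score contrast on the T0 imbalance were -0.70, -0.51 and -0.29. The adjusted slopes were about 0. Both estimators averaged about 0 under no effect, so neither is biased over randomizations.

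**The case against.** Difference-in-differences in a randomized trial is a valid, prespecified analysis and is right on average. This stands: the point concerns efficiency and behaviour given a chance imbalance, and these are largely two views of one thing, because the conditional shift is the source of the excess variance. It also stands that the size is assumed throughout, and that no change in an ICER or a recommendation has been shown.

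The cost covariates are not printed, since the text says only that the approach is similar. The first-difference example could also be read as successive differences, with T0 entering the first only. The ICER is nevertheless defined over T0 to T4, and the one covariate list that is printed has no T0 value. A full analysis plan would have to change that specification, not merely fill a gap.

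A reader might infer something stronger: that T0 resource use lacks the diary support of later visits, so that the economic contrasts are distorted. The Data collection section does say that falls, admissions and doctor contacts "are also documented in patient diaries to minimize recall bias", and diary falls are listed from T1 on. But nowhere does the article say that T0 resource use lacks a diary. Table 4 lists the same resource-use questionnaire at T0 to T4, and Table 10 names that questionnaire as the cost source. A recall shift equal in both arms cancels, and the EQ-5D is not diary-based. Under-capture at T0 would not enlarge the loss either if rho is held fixed. At k = 0.8 and rho 0.3 the variances are 1 + 0.64 - 0.48 = 1.16 and 0.91, a ratio of 1.27 against 1.54 with full capture. The documents do not support that reading.

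**Conclusion.** The point holds as a free improvement, not as an error in the plan. As printed, the utility model differences out T0 without adjusting for it, and the similar cost approach inherits this. At equal SDs, standard errors are 8% to 24% larger than the data require for rho 0.7 down to 0.3. Over the wider range of SD ratios examined, the variance ratio runs from 1.00 (no loss) to 2.10. All of this depends on rho and the SDs, which the article does not give.

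The point covers costs, EQ-5D index, EQ-VAS and Verbal Fluency Test. It does not cover falls, which have no T0 value. It gives no ground for calling the contrasts biased.

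**What to change.** Add the T0 value of the same measure to x_i: T0 cost in the cost model, and T0 EQ-5D index, EQ-VAS or Verbal Fluency Test score in the respective utility model. Modelling the follow-up value with T0 as a covariate is equivalent, because the arm coefficient under least squares is the same. Leave the falls model without a T0 term. Take the ICER simulation inputs from these adjusted models.

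The cost is one covariate per model. No new data, visits or patients are needed.
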